**Procedure:**

After assessment of eligibility and after the subject has signed the informed consent form, the subject will be enrolled in the study.

A **standard PrePex procedure** is described below:

The procedure will be carried out in a clean non-sterile environment. The subject will undergo sizing of the penis sulcus with the PrePex Sizing Plate. The penis will be cleaned by red Povidone-Iodine solution or other disinfection solution (Chlorahexidine, etc.) with the foreskin stretched backwards to expose the inner skin for the disinfection solution. Then the foreskin will be dried with a dry gauze. The Operator will then mark the circumcision line with a clean skin marker and then the Assistant will open the corresponding sized package of the PrePex device, and will load the Elastic Ring on to the Placement Ring. Then, Lidocaine 5% dermal cream will be applied on the inner foreskin. The Placement Ring with the Elastic Ring will be placed on the penis shaft and the foreskin tip will be stretched open to the sides by the operator hands, the operator may select to use a dry gauze to affirm the grip. Then, the Inner Ring will be applied through the stretched foreskin and over the glans penis (hereinafter, "glans") so that it will be placed fixed over the sulcus behind the glans (the base of the glans). At this point, the foreskin around the inner ring is held tight by the Assistant, and the Placement Ring and Elastic-Ring are approximated to the Inner Ring by the Operator. The foreskin is then adjusted to fit the circumcision marking line to the Elastic-Ring. Then, the Elastic-Ring is released from the Placement Ring on to the Inner Ring groove, initiating homeostasis. The procedure is then completed. Medication based on 400mg Ibuprofen is given to the subject to use at home if needed. The subject will then take part in a formal discharge session in a class room, where he will be instructed to return for a follow up visit and in any non sustained situation and to take painkillers in case of pain. The device will remain in situ for 7 days, at which the subject will return for a removal visit (i.e. if placed on Monday, removed on the following Monday). In case subjects arrive on day 5 or 6 and require removal of the device and foreskin, it is for the medical decision of the center managing physician to perform the removal if he/she thinks the removal is safe at this day. Those subjects will be followed for the procedure safety and efficacy. The foreskin is removed using sterile scissors, the Elastic Ring is removed using a #10 scalpel (surgical blade), and then the Inner Ring is extracted using a spatula or fingers, depending on the thickness of the foreskin. The area might be compressed with gauze for 30 seconds to avoid oozing and clear exudates. Following the removal process, the circumcision area will be dressed with a non-adherent sterile pad for 2 days, the subject will receive one dressing pad for home to change in case the dressing gets wet. The subject will then take part in a formal discharge session in a class room, where he will be instructed to turn to his local health center in any non sustained situation. Following the 2 days (day 9) the subject will remove the dressing on his own at home. The subject will be instructed to return in any non sustained situation, regardless of the follow-up visit.

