## 8.3 Statistical analysis

**Sample size:**

The intention is to obtain at least 100 evaluable subjects under Rwanda ethical responsibility (RNEC), determining to use the most deducted calculation setting and to maintain allocation ratio of 1:1:1 between the 3 study arms (33 per arm).

A sample size for the study was determined based on the two-sample t-test. In order to detect an effect size of 0.7 (Cohen's D) with 80% and at and a 5% level of significance between any two groups a sample size of 33 subjects is required. In the study each subject will have a smell test repeated by three different smellers this will be in order to examine the variability in odor sensation between different clinicians. Given this design and the three groups that will be compared, a statistically more powerful model (repeated measures ANOVA) is used instead of a t-test, and thus the study will be appropriately powered.

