## 8.3.1 General Considerations

The primary analysis will be performed on an intent-to-treat basis. Per-protocol analysis also will be performed as a secondary analysis. The required significance level of findings will be equal to or lower than 5%. All statistical tests will be two-sided. Where confidence limits are appropriate, the confidence level will be 95%.

All data will be presented via descriptive statistics. Binary data such as adverse events success/fail criteria will be presented as a count and percentage together with an exact 95% confidence interval. Adverse event rates will be compared descriptively with the reported rates of similar treatments. Continuous data will be represented by a mean, standard deviation, median, minimum and maximum together with 95% confidence intervals for the means.

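### Repeated measures ANOVA over smellers, the only model named, fits poorly with an intent-to-treat analysis when devices may come off before the Day 7 smell test

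*Protocol*

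**What the plan says.** The model appears only in the sample size text, in the synopsis and again in section 8.3. The design was sized on a simpler test ("A sample size for the study was determined based on the two-sample t-test") at an effect size of 0.7 with 80% power, and "a 5% level of significance between any two groups a sample size of 33 subjects is required". The text then says each man is smelled by three smellers and that "a statistically more powerful model (repeated measures ANOVA) is used instead of a t-test". Study day is not mentioned as a factor. No other inferential model is named; section 8.3.3 on the primary endpoint names none.

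Section 8.3.1 states: "The primary analysis will be performed on an intent-to-treat basis". Section 8.3.2.1 defines that population as the enrolled men who had the device placed.

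Odor is read on Day 0 and on Days 3, 5 and 7. On Day 7 the smell test comes before the foreskin and device are taken off (synopsis, Independent Blinded Reviewers). The procedure text in the synopsis and section 6.3 allows an exception, "In case subjects arrive on day 5 or 6 and require removal of the device and foreskin", at the managing physician's decision. Those men are followed for safety and efficacy, but no odor reading is described for them.

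**The concern.** Classical repeated measures ANOVA works on complete sets. A man lacking one smeller's reading is left out. A man whose device came off on Day 5 or 6 lacks the Day 7 reading from all three smellers. If the model has no day factor, nothing in it lets his earlier readings contribute. He belongs to the intent-to-treat population but not to the fit.

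What is at stake is mainly the comparison itself. If men with stronger odor are more likely to have the device removed early, and this happens more often in one arm, the men left on Day 7 are a selected group and the arm difference shrinks towards zero. A smaller cost is lost precision, in a design whose stated power leaves no margin.

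**Working it through.** **1. The plan's own figure.** Inputs from section 8.3: d = 0.7, 80% power, 5% level; section 8.3.1 makes tests two-sided. Normal approximation: n = 2(1.960 + 0.842)² / 0.7² = 15.70 / 0.49 = 32.04, rounded up to 33 per arm. The exact t calculation gives 33.02, with power 79.97% at 33. The stated 33 reproduces and is not in dispute.

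**2. Who is in the population and who is in the fit.**

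| Man | Intent-to-treat | Classical ANOVA on Day 7, smeller as repeat | Mixed model on all days |
|---|---|---|---|
| All three Day 7 readings | in | in | in |
| One Day 7 smeller reading missing | in | dropped | in |
| Device off on Day 5 or 6, no Day 7 reading | in | dropped | in, through earlier readings |

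The third row matters most. A mixed model over smellers on Day 7 alone would lose him too. Day has to be in the model.

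**3. Power if such men are dropped.** The documents give no loss rate, so a range is assumed. Two-sample t-test, d = 0.7, two-sided 5%, from 33 per arm, rounded down:

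| Assumed loss | Men per arm | Power |
|---|---|---|
| 0% | 33 | 80.0% |
| 5% | 31 | 77.4% |
| 10% | 29 | 74.5% |
| 20% | 26 | 69.7% |

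These figures treat each man as contributing one reading. If d = 0.7 refers to a single reading, the effect size for the mean of three smellers is 0.7 × √(3 / (1 + 2·ICC)). With an assumed ICC of 0.5 this is 0.857, and 80% power needs about 22 men per arm. With ICC 0.9 it is 0.725, and about 31 are needed. Averaging may therefore cover a modest loss.

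**4. Bias.** Simulation, 4,000 replicates. Assumptions: true Day 7 difference 0.70 SD, correlation 0.6 between days, removal likelier with higher Day 5 odor.

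| Early removal by arm | Complete-case estimate | Estimate using Days 3 and 5 |
|---|---|---|
| 15% vs 5% | 0.633 | 0.699 |
| 5% vs 5% | 0.697 | 0.696 |

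The first row is a shortfall of 0.70 − 0.633 = 0.067 SD, or about 10% of the effect.

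A second simulation (3,000 replicates per setting, 33 per arm, same correlation) used one removal rule for both arms, driven by Day 5 odor, so that the arm with stronger odor loses more men. The complete-case estimate was 0.669 with 94.8% of men complete, 0.645 with 89.2%, 0.624 with 82.5% and 0.606 with 72.2%. Using the earlier days gave 0.694 to 0.700.

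**The case against.** The strongest reply is that one phrase in a sample size justification is not an analysis specification. The analysis plan is not shown, and factors and missing-data rules commonly sit there. The name is also used for likelihood-based models that keep incomplete men, and the protocol nowhere says that such men are dropped. This stands against a reading that a colleague might draw, that the protocol cannot deliver intent-to-treat. It does not remove the point: the one model named, with the one repeat stated, fits badly with the stated population and the permitted early removal.

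A reader might also infer that Day 7 readings are lost by design. The text does not support that. Early removal is a case-by-case medical exception of unstated frequency. In the nurse cohort that the protocol summarises, one self-removal and one partial removal are reported among 590 men, although that listing may not capture every removal on Day 5 or 6. Nothing in the document supports 15% versus 5%; those rates are illustrative.

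A larger loss is tempting as well. Nine readings (three smellers on three days), each missing independently at an assumed 2%, would lose 1 − 0.98⁹ = 16.6% of men. But the stated repeat is the smeller, and a missed visit takes all three smellers' readings together. At 2% per visit, three visits give 1 − 0.98³ = 5.9%.

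Finally, once the foreskin is removed there is no Day 7 odor with the device in place. A mixed model then estimates a hypothetical value, and the simulations recover 0.70 because they take that value as the truth. This stands, and the fix has to say so.

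**Conclusion.** The point holds in a limited form. Read in its classical form with smeller as the repeat, the named model would turn the intent-to-treat comparison into a complete-case one for any man without a full set of Day 7 readings, and would leave his Day 3 and Day 5 readings unused.

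Bias needs two conditions that the protocol neither states nor excludes: removal related to odor, and removal differing by arm. Under the assumed 15% versus 5%, it is about 0.07 SD on a true 0.70; with equal 5% removal it is essentially nil. Power is the lesser matter: about 77% to 75% at 5% to 10% loss on a single-reading basis, possibly offset by averaging smellers. The sample size of 33 per arm is unaffected. This is worth correcting because the earlier readings are already planned, but it does not invalidate the design.

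**What to change.** In section 8.3 and the matching synopsis text, replace repeated measures ANOVA with a linear mixed model on all available odor readings. Use arm, day, arm-by-day and smeller as fixed effects, allow within-subject correlation across days and smellers, and take the Day 7 arm contrasts from this model.

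State that for men with early removal the contrast refers to Day 7 odor had the device stayed in place, assuming readings are missing at random given the earlier ones.

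The cost is protocol wording and standard software, with no added visits or data. The downside is reliance on the missing-at-random assumption, which the trial data cannot confirm.

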***Statistical Analysis:***

All data will be presented via descriptive statistics. Binary data such as adverse events success/fail criteria will be presented as a count and percentage together with an exact 95% confidence interval. Adverse event rates will be compared descriptively with the reported rates of similar treatments. Continuous data will be represented by a mean, standard deviation, median, minimum and maximum together with 95% confidence intervals for the means.

## 8.3.1 General Considerations

The primary analysis will be performed on an intent-to-treat basis. Per-protocol analysis also will be performed as a secondary analysis. The required significance level of findings will be equal to or lower than 5%. All statistical tests will be two-sided. Where confidence limits are appropriate, the confidence level will be 95%.

All data will be presented via descriptive statistics. Binary data such as adverse events success/fail criteria will be presented as a count and percentage together with an exact 95% confidence interval. Adverse event rates will be compared descriptively with the reported rates of similar treatments. Continuous data will be represented by a mean, standard deviation, median, minimum and maximum together with 95% confidence intervals for the means.

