**Study Duration:**

Study duration per subject will be up to 1 week (Placement visit and Removal visit after 7 days).

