**Primary Objectives:**

- Safety - To determine the adverse events rate per foreskin cleaning technique per study arm
- Efficacy - To compare the different odor levels when examine 3 arms of patients undergoing PrePex circumcision with same personal hygiene and with different foreskin hygiene techniques

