**Cohort Nurses Study:**

Background: This study represents the third and final clinical evaluation of PrePex device, performed in mid 2011 in Rwanda, based on World Health Organization suggested framework for evaluating Male circumcision devices, following the validation of safety, efficacy and supremacy over surgical circumcision performed by surgeons. The national goal in Rwanda is to offer voluntary male circumcision to 2 million men within 2 years to decrease HIV incidence, and this can only be achieved if nurses can safely conduct the procedure, as there are not enough physicians. It was assumed that the Adverse Event rate will be below 2%.

Methods: Rwanda National Ethics Committee approved the study. The study was conducted in Rwanda Military Hospital, Kigali Rwanda, between July 2011 to September 2011. 10 nurses with no previous knowledge on PrePex device were trained for 3 days on PrePex circumcision method. 590 healthy adult male volunteers were enrolled in the study and distributed between 5 teams of 2 nurses each. The device works by stopping flow of blood to the distal foreskin, leading to necrosis of the tissue, which is removed, along with the device, after 7 days in situ. The Placement and Removal procedures were bloodless, required no injected anesthesia, no sutures and no sterile settings. AE data, severity and relation to device was gathered throughout weekly visit for 8 weeks follow up, post Removal.

Results: All 590 male subjects achieved the endpoint of complete circumcision with glans fully exposed. There were 2 device related moderate AE (rate of 0.34%) including 1 case of bleeding 6 hours post removal that required 1 suture and 1 case of erroneous placement that partially disturbed urination flow, and required replacement. There were 2 non-device related AE (rate of 0.34%), both moderate, including 1 subject self removal and 1 subject partial removal of the device, contrary to specific instructions. All AE were easily resolved with simple intervention.

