3. STUDY ENDPOINTS

**Endpoints:**

**Primary Endpoint:**

- The primary endpoint is to assess the different odor levels by evaluating 3 arms of patients with different foreskin hygiene techniques.

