
**Follow-Up:**

The subjects will arrive for follow up visits on days 3, 5 & 7 in order to document the odor level.

There will be an interview phone call with the subject's partner (where possible) to assess hers perception of the smell. It will be conducted during days 5-6.

No follow up is required post Removal visit.

1. **Independent Blinded Reviewers (herein: Smellers):**

3 smellers will be chosen to participate in the study to perform a smell test using smell detector device; the "Nasal ranger" device, see the following link for technical information:

[http://www.nasalranger.com/Operations/Nasal%20Ranger%20Operations%20Manual%20v6.2.pdf](http://www.nasalranger.com/Operations/Nasal Ranger Operations Manual v6.2.pdf)

The Smellers will go through a short training in order to know how to operate the device and to assess their skills.

1. **Questionnaire for Subject:**

The subject's own perception of the smell will be documented and graded in VAS of 1-10 and compared to his normal perception of his smell and of the environment perceptive as he sees it.

The subject will also be questioned about his compliance to the required hygiene procedure of his study arm.

1. **Questionnaire for partners:**

The perception of the subject's spouse/partner will be documented where possible, via a phone interview.

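### The only adverse event comparison named is with unspecified outside rates, with no matched window, while the per-arm safety objective needs a contrast with the concurrent control arm

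*Protocol*

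**What the plan says.** Section 8.3.1 gives the AE analysis in two sentences, which also stand in the Synopsis and in section 8.3. The first covers presentation: "Binary data such as adverse events success/fail criteria will be presented as a count and percentage together with an exact 95% confidence interval". The second covers comparison: "Adverse event rates will be compared descriptively with the reported rates of similar treatments". The outside treatments are not named and no observation window is given for them.

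The second list of primary objectives in the Synopsis opens with "Safety - To determine the adverse events rate per foreskin cleaning technique per study arm". The first Synopsis list and section 2 give odor as the only primary objective. Section 3 does the same for the endpoint: "The primary endpoint is to assess the different odor levels by evaluating 3 arms of patients with different foreskin hygiene techniques".

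The schedule of events records AEs on Days 0, 3, 5 and 7. The Synopsis limits participation to one week, and the Follow-Up text in section 6.3 says "No follow up is required post Removal visit". In the clinical background, the nurse cohort is described differently: "AE data, severity and relation to device was gathered throughout weekly visit for 8 weeks follow up, post Removal".

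**The concern.** Two things are wrong with the comparison as written.

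First, it does not answer the objective. The device and the placement procedure are the same in all three arms; only the cleaning differs. A rate from another treatment or another PrePex series speaks to the device and the setting. It cannot separate out the effect of a syringe or of chlorhexidine. The randomised control arm can, but no AE contrast with it is stated.

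Second, the windows are not matched. A rate collected over one week of wear will tend to be lower than one that also covers weeks of healing, whatever the cleaning method does. The study aims at a cleaning procedure that lowers odor and keeps the circumcision safe. A favourable outside comparison could be read as support for that claim when it reflects only a shorter period of observation.

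**Working it through.** **Inputs, all from the protocol**
- Nurse cohort (section 1): 590 men, AEs collected weekly for 8 weeks after removal. There were 2 device-related AEs: a bleed 6 hours after removal, and an erroneous placement that needed replacement. There were 2 AEs not related to the device: a self-removal and a partial removal.
- Pivotal safety study (section 1): 50 men, with 1 mild AE after removal and no procedure-related AE between placement and removal.
- This trial: 33 men per arm, about 100 in all, with scheduled AE capture through the removal visit.

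**Step 1. Reproduce the quoted rate.** 2/590 = 0.339%, which rounds to the stated 0.34%. The exact (Clopper-Pearson) 95% CI is 0.04% to 1.22%.

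**Step 2. Cut the earlier data at removal.** The bleed drops out. I take the erroneous placement, the self-removal and the partial removal as wear-period events, which their nature implies.

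| Earlier data | Full window | Cut at removal |
|---|---|---|
| Nurse cohort, device-related | 2/590 = 0.34% (0.04 to 1.22) | 1/590 = 0.17% (0.00 to 0.94) |
| Nurse cohort, all AEs | 4/590 = 0.68% (0.19 to 1.73) | 3/590 = 0.51% (0.10 to 1.48) |
| Pivotal study | 1/50 = 2.0% (0.05 to 10.65) | 0/50 = 0% (0 to 7.11) |

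Each row moves down. The absolute shift is 0.34 − 0.17 = 0.17 points, 0.68 − 0.51 = 0.17 points and 2.0 − 0 = 2.0 points. In each row it comes from a single event. Section 9.2 defines an AE regardless of relation, so the all-AE row is nearer to what this trial will count. The pivotal study's AE has no stated relation to the device and no stated AE window, so that row shows direction only.

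**Step 3. What this trial could see against an outside rate.** If the true rate were 0.34%, the expected count in 100 men is 100 × 0.00339 = 0.34, and the chance of no event is (1 − 0.00339)^100 = 0.71. Zero events, and so a favourable-looking outside comparison, is likely from the sample size alone.

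**Step 4. Precision per arm.**
- With no events, the exact upper 95% limit is 1 − 0.025^(1/33) = 10.6%.
- With 1/33, the exact interval is 0.1% to 15.8%.

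**Step 5. What a between-arm test could do.** With 0/33 in one arm, Fisher's exact test gives p = 0.053 at 5/33 in the other and p = 0.024 at 6/33. With assumed true rates, its power is 6% for 2% against 10%, 48% for 2% against 20% and 71% for 2% against 25%. A test would add little; an estimate with its interval is the honest report.

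**The case against.** The strongest reply is that the documents do not say what the worst reading needs.

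- **The comparator.** A reader might infer that this trial's rates will be set against the 8-week rates. The protocol names no source, and the nurse cohort appears only as background. This stands: the bias is conditional on the source chosen.
- **The arms.** A reader might infer that the arms will not be set side by side at all. In fact the safety objective asks for a rate per arm, and section 8.3.1 gives exact intervals for binary data. A formal interval for a difference is detail that a SAP often supplies. This stands in part: what can be held against the protocol is that the one comparison it does name is the wrong one for its own objective.
- **Late events.** A reader might infer that nothing after removal can be recorded. The procedure text says "The subject will be instructed to return in any non sustained situation, regardless of the follow-up visit". Section 9.5 follows non-serious AEs to resolution, and section 10.3 follows ongoing device-related AEs for up to 30 days after the study. These routes depend on the man returning or on an event already known, so they soften the mismatch with weekly visits but do not remove it.
- **Slough and the late grading categories.** Section 9.2 lists slough, with possible onset on Day 9, among expected side effects outside the primary safety analysis, so missing it cannot bias the AE rate. The classification table is a general list for the device, and its post-removal categories do not contradict the schedule.
- **The randomised comparison.** All arms share one window, so stopping at removal does not by itself favour an arm. Delayed effects of cleaning would be missed in every arm.
- **Weight.** The outside comparison is descriptive and carries no decision rule.

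**Conclusion.** The point holds in a limited form. As written, the protocol compares AEs only with unnamed outside rates, which cannot show what the cleaning technique adds, and it does not match their window to a trial whose scheduled capture ends at removal. Against a source like the nurse cohort the result would lean towards safety: that cohort's device-related rate halves when cut at removal (0.34% to 0.17%), and its all-AE rate falls by a quarter (0.68% to 0.51%). In absolute terms this is about 0.2 points, resting on one event and on the assumption that such a source is used.

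That shift is small beside the trial's own uncertainty of 10.6% or more at the upper limit per arm. It would be tempting to set 10.6% against 0.34% and call the gap bias, but that divides a confidence limit by a point estimate and reflects 33 men per arm, not the window. Nor do the documents show that two of every three earlier AEs came after removal: counting the two wear-period events not related to the device, it is 2 of 5 across the two studies.

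Separately, the primary objective lists disagree on whether safety is primary, so the standing of the AE analysis is unclear.

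**What to change.** 1. Replace the comparison sentence in the Synopsis, section 8.3 and section 8.3.1 with wording such as: *AE rates from placement through the removal visit are reported per arm as count, percentage and exact 95% CI. Arm 2 minus Arm 1 and Arm 3 minus Arm 1 are given descriptively with exact 95% CIs for the difference. Events reported after the removal visit are listed separately by arm.*
2. Drop the outside comparison, or limit it to named sources and to their events between placement and removal.
3. State that the safety conclusion covers placement through removal (nominally Day 0 to Day 7) only and that precision is low. Give the interval that belongs to the observed count: 0/33 allows a rate up to 10.6%, and 1/33 up to 15.8%.
4. Make both Synopsis lists, section 2 and section 3 agree on whether safety is primary.

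The cost is wording and one extra table, with no added visits or men. The intervals will be wide at 33 per arm, so the safety claim becomes more modest. Whether men should be followed for longer is a clinical matter and is not proposed here.
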